**Methods and analysis:**

Patients diagnosed with a TIA or a minor stroke are being recruited at the emergency or neurology departments of the Hospital Pedro Hispano, located in Matosinhos, Portugal (n=70). Those who accept to participate will be randomly allocated to two groups (1:1): (a) Intervention—receives a 3 months combined approach, initiating early post-event, composed of cognitive training, physical exercise, nutrition, psychoeducation and assessment/correction of hearing loss; (b) Control—participants will not be subject to any intervention. Both groups will receive the usual standard of care provided to these diseases. Recruitment began in May 2022 and is expected to continue until March 2023. Socio-demographic characteristics, lifestyles, health status, cognitive function, symptoms of anxiety and depression and quality of life will be assessed; as well as anthropometry, blood pressure and physical condition. Time to complete or partial recovery of instrumental activities of daily living will be assessed using an adapted version of the Frenchay Activities Index. All participants will be evaluated before the intervention and after 3 months.

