## Methods and analysis

### Study design

The present study is a two-arm parallel, superiority, pilot randomised controlled trial (RCT), which will be nested in the ongoing project ‘Multiple Interventions to Prevent Cognitive Decline’ (MIND-Matosinhos).^16^ This proposed pilot study will provide crucial information about the logistic feasibility, provide estimates of eligibility, recruitment and attrition rates, optimising the study design. It will also enable a greater precision in the power and sample size calculations of a future full-scale study.

The primary endpoints will be the feasibility of this multidomain programme, as well as the time to recovery to pre-event functionality after the occurrence of a TIA or a minor stroke. A block randomisation with a 1:1 allocation will be performed.

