### Intervention

The intervention will be implemented over 3 months and will comprise five different components, including cognitive training, physical exercise, nutritional education, psychoeducation and assessment and correction of hearing problems. Only the intervention group will be exposed to all or any of the components of this comprehensive intervention programme. Both groups will continue to receive the usual standard of care provided to this type of clinical disease in the hospital setting. The usual standard of care consists of the initiation of the appropriate secondary prevention and referral to the outpatient cerebrovascular diseases clinic (telephone call at 1-month post-event and in-person appointment at 3 months post-event). Depending on the clinical presentation and neurological deficits, patients can also be referred to an outpatient physical medicine and rehabilitation appointment.

Since early intervention post-vascular event is decisive, given the time interval between neurological injury and the onset of nervous function recovery activities, intervention sessions are aimed to begin within no later than 15 days after the cerebrovascular event. Considering this timeline, once the participants are recruited and randomised, the intervention will start immediately, especially cognitive training.

To minimise refusals and losses to follow-up, all evaluations and sessions will be scheduled by the participant’s preference. A written plan with the intervention schedules will be given and sessions reminded through email or phone messages in the day before (day, time and location). If one intervention session is missed, efforts will be placed to arrange another suitable time in another group and individualised meetings will be rescheduled. If not possible, the missed appointment will be documented, and the dropout or non-compliance reasons will be registered for further analysis.

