### Primary outcome measures

The primary outcomes for the study are related with its feasibility and time to partial or complete recovery of each instrumental ADLs.

To evaluate the feasibility of this study, the following primary outcomes will be assessed:

Recruitment time frame: proportion of participants recruited within 7 days after onset of symptoms. It will be assessed by dividing the number of participants recruited within the time frame divided by the total number of participants.Beginning of the intervention: proportion of participants that started any of the interventions no later than 15 days after onset of symptoms.Adherence to each component of the intervention: proportion of adherence to each component of the intervention and different intervention modalities (remote/in person), calculated as the number of sessions attended divided by the total number of sessions provided. For the COGWEB training, the outcome will be the absolute number of sessions.Dropout: proportion of participants who dropped out of the study, calculated as the number of participants who dropped out after attending at least one session divided by the total number of participants who attended at least one session.

Time to recovery in each instrumental activity of daily living will be measured by an adapted version of the Frenchay Activities Index (FAI). The translated and validated version of the FAI—adapted version for the Portuguese population^23^ will be used to assess the instrumental ADLs functional performance at baseline and follow-up at 3 months. The version used in this study is based on the perception of the patient’s capacity to perform a specific instrumental ADLs instead of its frequency, as stated in the original scale developed by Holbrook and Skilbeck.^24^ The scale consists of 15 activities, scored from 1 to 4 (1-could not do at all; 2-very difficult; 3-a little difficult; 4-not difficult at all).^23^ Although the original index suggests that total scores for men and women should be considered separately,^24^ in the present study the score of each activity will be analysed independently, as the interest in exploring the impact of the programme in each activity.

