### Secondary outcome measures

Secondary outcomes and the instruments that will be used for their assessments are described in tables 1 and 2. Briefly, secondary endpoints related with the study’s feasibility will be measured, namely time of follow-up, implemented sessions and complete assessment of participants (table 1). Additionally, cognitive function, quality of life, symptoms of anxiety and depression, as well as functional capacity to perform basic ADLs will be evaluated through questionnaires validated for the Portuguese population (table 2). Physical condition, blood pressure and anthropometrics will be ascertained by trained interviewers. Levels of glycated haemoglobin, and 24-hour urinary excretion of sodium and potassium will be also measured. The secondary outcomes described on the table 2 will be also measured at baseline and follow-up at 3 months.

**Table 1 T1:** Description of the secondary feasibility outcomes

Outcome	Description
Time of follow-up	Calculated by the number of days between the participant’s first and last session attended.
Implemented sessions	Proportion of sessions implemented, calculated as the number of sessions that the research team was able to implement divided by the total number of sessions planned.
Complete assessment of participants	Proportion of participants with full information at baseline and follow-up points, calculated by dividing the number of participants with complete information by the number of participants evaluated.

**Table 2 T2:** Description of the instruments used for the evaluation of secondary outcomes

Outcome	Instrument	Description
Cognitive performance	MoCA^29–31^	Brief screening tool to detect mild cognitive impairment. It assesses eight cognitive domains: visuospatial ability, executive function, attention, concentration, working memory, language, verbal memory and orientation, with scores from 0 to 30. Higher scores represent better cognitive performance, and one point is added for participants with less than 12 years of education.
	Brain on Track^21 32^	Self-administered computerised cognitive test for remote longitudinal assessment. It evaluates different cognitive domains through exercises, such as attention, memory, executive functions, language, calculation, constructive capacity and visuospatial processing. The score range is the maximum number of correct answers within a limit of time. Higher scores are representative of better cognitive performance.

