### Data analysis and sample size

The associations between the social and clinical characteristics and feasibility (eg, recruitment time frame, adherence, dropouts) and lifestyle outcomes will be quantified through linear or logistic regression models, as applicable. Time in days from the onset of symptoms to complete or partial recovery in each instrumental ADLs will be estimated and illustrated by Kaplan-Meier survival curves. The time comparison between intervention and control groups will be made through the log-rank test. To estimate the association between the intervention and the recovery time, HRs will be estimated, through the computation of univariate and multivariate Cox regression models.

Training of the interviewers and use of standardised procedures for data collection is expected to contribute to a low proportion of missing data, and no imputation is being planned.

To the best of our knowledge, there is no previous information regarding effect sizes and SDs regarding the primary outcome related with the recovery of functionality after a TIA or a minor stroke. Nevertheless, a sample size of at least 70 participants (35 per arm) is commonly recommended for a pilot study when estimating the pooled SD.^25^ Nevertheless, taking into account the results of a previous RCT evaluating a cardiac model of rehabilitation for reducing risk factors post-TIA and stroke,^26^ this sample size will allow to detect mean differences of 5.5 and 6.0 in the changes observed in the Hospital Anxiety and Depression Scale—anxiety and depression scores, respectively, between intervention and control groups (assuming a statistical power of 80% and a level of significance of 5%).

To achieve the sample size needed to accomplish the proposed objectives, we expect to invite approximately 100 individuals, since a participation of 70% was previously observed in the EPIPorto cohort.^27^ We also expect a dropout of 10% from baseline to the first follow-up; nevertheless, and in order to minimise refusals and losses to follow-up, all activities will take place near participants’ residence and be scheduled for their convenience.

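### The primary dropout outcome is labelled as dropout from the study but measures only programme discontinuation among intervention-arm starters, so it does not estimate the attrition the pilot sets out to measure

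*Protocol article*

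**What the plan says.** Under Primary outcome measures, one of four primary feasibility outcomes is introduced as "Dropout: proportion of participants who dropped out of the study". The formula that follows counts those who "dropped out after attending at least one session divided by the total number of participants who attended at least one session".

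Who can attend a session is settled elsewhere in the article:

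- The Intervention section states: "Only the intervention group will be exposed to all or any of the components of this comprehensive intervention programme".
- The Abstract says of the control group that "participants will not be subject to any intervention".
- The Intervention section names evaluations separately from sessions, so an assessment visit is not a session.
- The Randomisation section places allocation after the baseline assessment, and so before any session.

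Two passages set out what the figure is needed for. Study design says the pilot will "provide estimates of eligibility, recruitment and attrition rates" in preparation for a full-scale trial. Data analysis and sample size adds: "We also expect a dropout of 10% from baseline to the first follow-up". That expectation is not limited to one arm or to people who attended sessions.

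Two secondary feasibility outcomes in Table 1 are related. Complete assessment is "calculated by dividing the number of participants with complete information by the number of participants evaluated". Time of follow-up counts days between the "first and last session attended".

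**The concern.** The label and the formula describe different quantities. The label promises loss from the trial. The formula gives the share of programme starters who later stop.

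A full-scale trial needs the proportion of randomised participants without the 3-month outcome, in each arm. That proportion drives the inflation of the sample size, and the contrast between arms warns of bias. Participants here cannot be blinded, so control participants might leave at a different rate from those offered the programme. A ratio that no control can enter will not show this.

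The outcome also omits people allocated to the programme who never attend, although they matter for feasibility. And it cannot be set against the protocol's own 10% planning figure, which runs from baseline to follow-up.

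**Working it through.** **Inputs from the article.** About 100 people invited with 70% participation, 35 per arm, and 10% expected dropout from baseline to first follow-up (all from Data analysis and sample size).

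**The plan's own figures.** 100 × 0.70 = 70 participants, which matches the stated sample of 35 per arm. Ten per cent of 70 is 7 lost, leaving 63.

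**The two measures.** Let s be intervention participants who never start, d those who drop out after at least one session, and c control participants lost.

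- Outcome as written: d / (35 − s).
- Attrition among all randomised: (s + d + c) / 70, if everyone counted in s, d and c misses the 3-month assessment.

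The article does not give s, d or c. The counts below are assumptions, chosen to show how the two measures can separate.

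| Assumed s, d, c | Outcome as written | Intervention arm | Control arm | Overall |
|---|---|---|---|---|
| 0, 0, 7 | 0/35 = 0% | 0/35 = 0% | 7/35 = 20.0% | 7/70 = 10.0% |
| 5, 3, 3 | 3/30 = 10.0% | 8/35 = 22.9% | 3/35 = 8.6% | 11/70 = 15.7% |
| 0, 3, 0 | 3/35 = 8.6% | 3/35 = 8.6% | 0/35 = 0% | 3/70 = 4.3% |

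- In the first row the outcome reports no dropout, although overall attrition is exactly the planned 10%.
- In the second row it reads 10%, apparently confirming the planning figure, while overall attrition is 15.7% and the arms differ.
- In the third row it is twice the overall figure.

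Over a grid of s from 0 to 7, d of 0 or 3 and c from 0 to 7, the outcome stays between 0% and 3/28 = 10.7%, while overall attrition runs from 0% to 17/70 = 24.3%.

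**Sensitivity to the 3-month assumption.** A never-starter may still attend the 3-month assessment. If all five in the second row did, attrition would be (3 + 3)/70 = 8.6%, and the outcome as written would still be 10%. The ratio does not respond to whether those people are retained.

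**Precision.** With all randomised as denominator, 7/70 = 10% has an exact (Clopper-Pearson) 95% interval of 4.1% to 19.5%. The ratio as written has a denominator of at most 35. At 3/30 = 10% the interval is 2.1% to 26.5%.

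**The case against.** The strongest reply is that attrition can still be obtained. Everyone is assessed at baseline, before randomisation, and again at 3 months, so loss over that interval is observable in each arm, and it is the same interval as the 10% planning figure. This stands. A reader might infer that the pilot is unable to estimate attrition or to check its own assumption; the article does not support that. What cannot do so is the outcome that carries the name.

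Second, never-starters are not wholly invisible. The primary outcome on starting within 15 days of symptom onset would naturally count them as failures, and the protocol records reasons for dropout and non-compliance. This also stands in part. However, that outcome pools late starters with never-starters and says nothing about controls.

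Third, the complete-assessment outcome might fill the gap. If the participants evaluated are all those with a baseline evaluation, its denominator is close to all randomised. A reader might instead take them to be those seen at 3 months, so that losses leave the denominator. The wording permits either reading, so no firm figure can be attached to that ambiguity. On either reading the outcome mixes loss to follow-up with incomplete data.

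Fourth, the session-based formulas are legitimate for what they measure. Discontinuation among starters is worth reporting, and first-to-last-session time is a usable measure of duration in the programme, although it is undefined for controls.

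Finally, a journal article leaves detail to the full protocol or analysis plan. That does not help here, because the numerator and denominator are stated explicitly.

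**Conclusion.** The point holds for the definition as written. The primary dropout outcome excludes all controls and all randomised never-starters, so it is neither dropout from the study nor comparable with the 10% assumption, and it cannot show differential attrition.

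It is tempting to say that it understates attrition. It may, but not necessarily: the error runs in either direction depending on where the losses fall, as the first and third rows of the table show. The size of the gap rests on assumed counts and, for the overall figures, on those participants missing the 3-month assessment. The exclusions themselves follow from the article's text and need no assumption.

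The fault affects a reported primary feasibility result and its use in planning the full trial. It does not affect the comparison of recovery times, and it can be repaired with data already planned.

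**What to change.** - Define study attrition as randomised participants without a 3-month assessment, divided by all randomised. Report it overall and by arm, with exact 95% confidence intervals.
- Keep the present ratio, renamed programme discontinuation among starters.
- Report never-starters as a proportion of all those allocated to the intervention.
- State in Table 1 that the denominator for complete assessment is all randomised participants.

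No new data are needed. The cost is a change to a primary outcome definition after recruitment began on 11 May 2022. It may count as a substantive amendment, which the Ethics and dissemination section says goes to the Ethics Committee. The resulting figures may also look less favourable than those from the present definition.

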### Eligibility criteria

Patients aged 18–85 years old and with a clinical diagnosis of TIA or minor stroke as defined by an NIHSS score ≤3 are eligible for this study. Additional inclusion criteria include: the onset of symptoms within the last 7 days; first-time stroke or TIA; at least 4 or more years of education; discharged home without the need for inpatient rehabilitation; modified Rankin Scale (mRS) 0–2. Patients will be excluded if they are unable to attend the face-to-face intervention sessions, or if they have: previous diagnosis of dementia or severe disability; contraindication for physical exercise, severe loss of hearing, vision or communication skills; frailty, reduced life expectancy due to severe disease or need for regular treatments that compete with availability for intervention (eg, chemotherapy, haemodialysis).

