For the present study, only activities that are part of participants’ daily lives will be considered, namely those that were performed at least once in the last 12 months. Time to recovery will be defined as the time from the start of the intervention programme to the time of complete or partial recovery. Each participant will report their level of performance in each activity at the baseline and follow-up at 3 months. In the baseline, if a participant scores a specific activity as altered (score 1–3), their level of performance before the TIA or minor stroke will be confirmed to understand if the change in the activity performance is related with the cerebrovascular event. It will be also inquired and recorded the date when a difficulty in a certain activity ceased. The average of activities altered post-event (score 1, 2, 3) at baseline and the average of activities that improved in both groups on completing the intervention programme will be measured.

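### The primary time-to-recovery outcome has two different starting points, and one of them, programme start, does not exist for the control arm

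*Protocol article*

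**What the plan says.** **Outcome definition.** The protocol article, under Primary outcome measures, states: "Time to recovery will be defined as the time from the start of the intervention programme to the time of complete or partial recovery".

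**Analysis.** Under Data analysis and sample size, the quantity shown by Kaplan-Meier curves is "Time in days from the onset of symptoms to complete or partial recovery in each instrumental ADLs". The arms are then compared by a log-rank test and by univariate and multivariate Cox models.

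**Design.** Study design names the endpoint as "the time to recovery to pre-event functionality after the occurrence of a TIA or a minor stroke", which sets no explicit time zero.

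**Who has a programme start.** The Abstract says that control "participants will not be subject to any intervention". The Intervention section says "Only the intervention group will be exposed to all or any of the components of this comprehensive intervention programme". No substitute start date is given for controls.

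**Timing.** Eligibility requires "the onset of symptoms within the last 7 days". Randomisation follows the baseline assessment. For the programme, "intervention sessions are aimed to begin within no later than 15 days after the cerebrovascular event". That limit is a target: the proportion of participants who meet it is itself a feasibility outcome, and the Contingency plan accepts that the time frame may be hard to attain.

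**The concern.** A time-to-event comparison needs one time zero, defined the same way in both arms and available for everyone randomised. The article gives two, and the one in the formal outcome definition exists in only one arm. An analyst who follows that definition must either invent a date for controls or abandon it for the origin in the analysis section.

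This affects more than wording. Effectiveness on time to recovery is a primary objective, the arms are to be tested on it, and the pilot is meant to inform the power and sample size of a full-scale trial. A hazard ratio or median measured on an unclear clock would carry into that design. If the choice of origin is left until the data are seen, it can also influence the result.

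**Working it through.** The article gives no effect size or power figure for time to recovery, so there is no stated number to reproduce. The check is of the definitions, followed by what a mixed clock would do.

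**1. Which dates exist.** Let T be the day of recovery counted from onset, R the day of randomisation (after baseline) and S the day the programme starts.

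- T from onset: exists in both arms.
- T − R: exists in both arms.
- T − S: exists only for intervention participants who start.

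**2. How far apart the origins are.** Take R = 7 and S = 15, the limits for recruitment and for the programme-start target, and an assumed recovery on day 45:

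- from onset: 45 days
- from randomisation: 45 − 7 = 38 days
- from programme start: 45 − 15 = 30 days

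The recovery is identical, but its recorded time differs by up to 15 days. In a follow-up of about 91 days that is 15/91 = 16%. With S = 15, an assumed recovery on day 12 gives 12 − 15 = −3 days, which is not a valid survival time. The article does not say how such a case is handled.

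**3. Why a common origin is safe under the null.** Randomisation comes after onset and baseline. With no treatment effect, T and T − R each have the same distribution in both arms. This remains true if the analysis keeps only activities still altered at baseline, because that selection precedes allocation. T − S in one arm against T or T − R in the other does not have this property.

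**4. Null simulation.** None of these inputs is in the article:

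- recovery identical from onset in both arms, Weibull shape 0.7 or 1.0, median 20, 30 or 45 days
- baseline uniform on days 0 to 7, programme start uniform from baseline to day 15
- censoring 91 days after baseline
- 35 or 20 evaluable participants per arm, 600 runs per setting

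A hazard ratio above 1 means apparently faster recovery in the intervention arm. False benefit is the share of runs significant in that direction, nominally 2.5%.

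| Intervention clock | Control clock | Recoveries before programme start | Null HR | False benefit |
|---|---|---|---|---|
| Programme start | Onset | Counted at about day 0 | 1.13–1.40 | 5%–26% |
| Programme start | Baseline | Counted at about day 0 | 1.08–1.23 | 3%–13% |
| Programme start | Onset | Dropped | 0.95–1.19 | 2%–8% |
| Programme start | Baseline | Dropped | 0.90–1.04 | 1%–4% |
| Onset, or baseline | Same as intervention | Not applicable | 0.98–1.03 | 2.0%–4.7% |

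In the first row the intervention median is 7 to 11 days shorter with no true effect. In the last row the Monte Carlo error of the false-benefit rate is about 0.6 to 0.9 percentage points, and the hazard ratio shows no systematic shift.

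**The case against.** The strongest reply is that the only section specifying the log-rank and Cox analysis names a single origin, onset, which every participant has. Applied as written, it keeps never-starters and gives no between-arm bias from the clock. That stands. In a separate null simulation with 6,000 participants per scenario, hazard ratios with onset in both arms and with randomisation in both arms differed by at most 0.01 in all 18 scenarios.

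It follows that several stronger readings are not supported:

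- **That the planned comparison is biased towards benefit.** This needs a different clock in each arm, which the article does not prescribe. The direction also depends on how recoveries before programme start are handled, on which it is silent.
- **That hazard ratios could reach about 2.** Such values need a rising recovery hazard and a short median, neither of which the article supports. It also says that the programme starts immediately after randomisation. With assumed starts 0 to 2 days after baseline and controls timed from randomisation, the null hazard ratio is only 1.03 to 1.07, even with early recoveries counted.
- **That onset is itself a biasing origin.** If only activities still altered at baseline are analysed, the days from onset to baseline are event-free, which distorts the Kaplan-Meier curves. It does so equally in both arms. The restriction itself is inferred from the outcome section and is not stated there.
- **That never-starters will be excluded.** No rule says so. They simply have no time under the programme-start definition.
- **That the 3-month visit is timed differently by arm.** Nothing in the article says this.

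It is also fair that this is a pilot with co-primary feasibility aims and no power claim for this outcome. That limits the consequences, but it does not remove the contradiction.

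**Conclusion.** The point holds as a contradiction within a primary outcome. The two sections state different origins, and the one in the formal definition cannot be applied to controls or to intervention participants who never start. That conclusion rests on the text alone.

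The size of any harm is conditional. It arises only if the two arms are timed from different dates. Under the assumptions listed, the null hazard ratio is then about 1.1 to 1.4 when recoveries before programme start count as early events, and 0.90 to 1.19 when they are dropped. A single clock in both arms, whether onset or baseline, removes the artefact. The definition should be corrected before any between-arm analysis.

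**What to change.** State one origin, the same in both arms, in both Primary outcome measures and Data analysis and sample size. The date of randomisation is preferable: everyone randomised has it, it follows baseline, and it does not depend on whether the programme was started. Baseline, or onset with entry at baseline, would also work.

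Say that the analysis of each activity includes all randomised participants in whom it was altered at baseline because of the event, whether or not they started the programme. A recovery between randomisation and programme start then counts on its actual date.

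If times from onset are also to be shown, use delayed entry (left truncation) at the baseline date, so that the curves do not begin with days on which no recovery could be counted.

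The cost is about two sentences and no new data: randomisation gives each participant a date, and onset is already taken from the medical record. The timing of the 3-month assessment need not change on this account.

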Taken together, these findings highlight the importance of multidomain interventions aiming to promote functioning levels among patients with TIA or minor stroke, and to develop preventive actions and health promotion plans specifically designed for this group. As such, this pilot study primarily aims to explore the feasibility and the effectiveness of an innovative multidomain intervention programme, composed of five strategies: cognitive training, physical exercise, nutrition education, psychoeducation and assessment/correction of hearing problems. These are aimed at accelerating the return to pre-event functionality in patients with a TIA or a minor stroke diagnosis. The primary objectives are as follows:

To assess the feasibility of methodology for early recruitment, collecting information and delivering the interventions.To estimate the effectiveness of this programme on the time to recovery in each instrumental ADLs.

As secondary objectives, the effect of this intervention on cognitive function, adherence to the Mediterranean diet, physical function, basic ADLs, symptoms of anxiety and depression, quality of life, anthropometric measures and blood pressure, will be also assessed.

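### The timed primary event includes partial recovery, but the only date described is when the difficulty ceased, and partial recovery is not defined

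*Protocol article*

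**What the plan says.** In the Protocol article, *Primary outcome measures* names the "time to partial or complete recovery of each instrumental ADLs" as a co-primary outcome beside feasibility, and defines it as "the time from the start of the intervention programme to the time of complete or partial recovery". Each of 15 activities is scored "1-could not do at all; 2-very difficult; 3-a little difficult; 4-not difficult at all". Scores 1 to 3 at baseline count as altered, and for those activities the level before the event is confirmed. There are two scoring occasions: "Each participant will report their level of performance in each activity at the baseline and follow-up at 3 months". One event date is described: "It will be also inquired and recorded the date when a difficulty in a certain activity ceased". The section also plans average numbers of altered and improved activities, which need no date.

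*Data analysis and sample size* applies Kaplan-Meier curves in days, the log-rank test and Cox models to complete or partial recovery of each activity. No section says which change on the 1 to 4 scale counts as partial. The *Introduction* gives the aim as "accelerating the return to pre-event functionality in patients with a TIA or a minor stroke diagnosis".

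**The concern.** The event and the date recorded for it do not correspond. The event is reached by a partial improvement, whereas the date marks the end of the difficulty. Anyone who improves but still has some difficulty has met the event definition without a described time. The analyst must then choose: censor these participants, place them at the 3-month visit, or treat them as interval-censored. The three choices give different curves and possibly different hazard ratios.

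A comparison of speed is at stake. If the programme mainly turns partial into complete recoveries, the intervention arm will have more dated events. That could look like faster recovery even when first improvement comes equally early in both arms. *Study design* says the pilot is meant to sharpen the sample size of a full-scale trial, so such an artefact would be carried forward.

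**Working it through.** **Step 1. Upward changes on the scale.** Take any improvement as partial recovery (an assumption, since the article gives no definition).

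| Change, baseline to 3 months | Difficulty gone? | Described date |
|---|---|---|
| 3 to 4 | yes | is the event date |
| 2 to 4, 1 to 4 | yes | is the event date if in one step; later than first improvement if in stages |
| 1 to 2, 1 to 3, 2 to 3 | no | none described |

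Three of the six possible improvements have no described date, two may be dated late, and one is unaffected. The problem is confined to activities scored 1 or 2 at baseline. A related case is an activity with a confirmed pre-event score of 3 that falls to 1 and regains 3. It has fully returned to its earlier level, yet the difficulty never ceased.

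**Step 2. What the analysis needs.** Kaplan-Meier, log-rank and Cox in their usual form need an exact or right-censored time. For a partial recovery the two scores show only that the event fell between baseline and 3 months. For a stepwise recovery ending at 4, the first improvement lies between baseline and the recorded date.

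**Step 3. Size.** The article gives no recovery rate, event count or share of partial recoveries for this outcome, so there is no stated figure to reproduce. The inputs below are assumptions.

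*Illustration A.* Exponential time to first improvement, 70% improved by day 90, and a share q of improvers partial only. True recovery by day 45 is 1 − √0.30 = 45%. Recorded recovery before the visit is (1 − q) times the true value.

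| q | Day 45, recorded (true 45%) | Day 90, partials censored (true 70%) | Day 90, partials placed at visit |
|---|---|---|---|
| 0 | 45% | 70% | 70% |
| 20% | 36% | 56% | 70% |
| 40% | 27% | 42% | 70% |
| 60% | 18% | 28% | 70% |

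*Illustration B.* Exponential with a median of 30 days and partial recoveries placed at day 91. The proportion improved by day 91 is 1 − 2^(−91/30) = 0.878.

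- q = 25%: the recorded median solves 0.75 × (1 − 2^(−t/30)) = 0.5, so t = 30 × log2(3) = 47.5 days. The step at the visit is 0.25 × 0.878 = 22 points.
- q = 50%: the curve reaches only 0.50 × 0.878 = 44% before the visit. The recorded median is therefore day 91, with a 44-point step.

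*Two arms under B.* Let first improvement be equally fast in both arms, with q = 50% in control and 25% in intervention. True day-45 recovery is 1 − 2^(−1.5) = 65% in both. The recorded values are 0.50 × 0.646 = 32% and 0.75 × 0.646 = 48%. This shows the mechanism and does not predict the trial's result. No log-rank test or hazard ratio was simulated.

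**Step 4. Dated events.** From 70 participants with the article's 10% dropout, 63 remain. If half have a given activity altered and 70% of those improve (both assumed), 63 × 0.5 × 0.7 = 22 events occur. Those with a cessation date number 18, 13 or 9 at q = 20%, 40% or 60%. With the Schoenfeld approximation, power = Φ(√d × ln 2 / 2 − 1.96) for an assumed hazard ratio of 2. It is 37% with 22 events and 31%, 24% or 18% with the dated ones.

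**The case against.** - **The article does not say that this is the only date.** The sentence says the date is recorded as well, and a condensed article may leave item-level questions to the full protocol or the case report form. This stands as a caution: a reader might infer that partial recoveries certainly go undated, and the text does not establish that. Even so, the article is not silent here. It states both an event and a date, and the two do not match. Reading the end of a difficulty as the end of one grade of difficulty is possible but strained.
- **The curves need not be wrong.** Partial recoveries are visible from the two scores and could be analysed as interval-censored. This also stands. The article describes only the standard methods, however, so bias is a risk that depends on handling, and it vanishes if no one recovers only partly.
- **The population is mild.** Participants have NIHSS ≤3 and mRS 0–2 and go home without inpatient rehabilitation. Many altered activities may score 3, where the described date is the event date. The assumed shares may therefore be too high; the article gives nothing to settle this.
- **Counting partial recovery is a choice.** A reader might infer from the aim of returning to pre-event function that a composite with partial recovery is an error. The abstract, outcome and analysis sections use it consistently, so it is a legitimate design choice. What is missing is a definition and a matching date.
- **Recall bias is already acknowledged**, in the strengths and limitations. That concerns inaccurate dates and does not cover an event for which no date is described.

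**Conclusion.** The mismatch holds as a conflict between two stated rules. The event is complete or partial recovery, the described date fits complete recovery to score 4, and partial recovery has no operational meaning. Followed as written, some activities scored 1 or 2 at baseline will have no event time, and others a late one if first improvement is the event. Standard survival results may then be biased in proportion to the share of partial recoveries. In the assumed scenarios, day-45 recovery falls from 45% to between 36% and 18%, and unequal shares between arms can create an apparent difference in speed. The documents do not support the stronger statement that the curves will be wrong. The share of partial recoveries, their coding and any further date questions are not given. The point still matters for a primary outcome of a pilot already recruiting, because a date not asked for at the 3-month assessment is hard to recover later.

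**What to change.** Make the event and its date agree, in one of two ways.

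**(a)** Limit the time-to-event outcome to return to the confirmed pre-event score, and record the date that score was regained. Where the pre-event score was 4, this is the date already asked for. Analyse partial improvement as a 3-month outcome from the two existing scores. Cost: fewer timed events (18, 13 or 9 instead of 22 per activity under the assumptions above).

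**(b)** Keep partial recovery in the event and define it on the 1 to 4 scale. At the existing blinded 3-month assessment, ask for the date of first improvement in each altered activity. Treat partial recoveries that remain undated as interval-censored between baseline and 3 months. Cost: one more recalled date per altered activity, and a change to the forms after recruitment has begun (11 May 2022).

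The usual-care contacts ("telephone call at 1-month post-event and in-person appointment at 3 months post-event") should not be used to collect these dates. The article describes them as clinic care and does not show that they are made by the blinded interviewers. Whichever option is taken, *Primary outcome measures* and *Data analysis and sample size* should state the same event. Those two sections also differ on the time origin, which is a separate matter.
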